# Outcomes

## Unplanned liver-related hospital admission rate

Unplanned liver-related hospital admission rate will be the primary outcome measure of the trial. Other hospitalization measures, as outlined in the Aims section, will be measured as secondary endpoints.

## Incremental cost effectiveness relative to usual care and quality of life

The economic evaluation will be carried out to assess the incremental cost effectiveness of the CDM model, relative to usual care, for patients with decompensated cirrhosis over the study duration. The primary economic outcome will be the incremental cost per unplanned admission avoided in the intervention arm relative to the usual care arm. Secondary economic outcomes will include the incremental cost per death prevented and incremental costs per quality adjusted life year (QALY) gained. QALYs will be based on responses to the EuroQoL 5 dimensions 5 level (EQ5D 5L) and a validated disease specific Chronic Liver Disease Questionnaire (CLDQ)([43](#_ENREF_43)).

Incremental costs associated with the intervention compared to usual care over the study period will be estimated using Medical Benefits Schedule (MBS) and Pharmaceutical Benefits Schedule (PBS) data to estimate primary care, pharmaceutical, and private hospital costs, and centralised costing data for inpatient episodes at public hospitals (Australian Refined Diagnosis Related Groups (AR-DRGs) cost weights). Consent to access PBS/MBS/AR-DRG data will be sought from recruited patients. Intervention specific costs (e.g. labour costs, travel and telephone expenditure etc) will be collected administratively within the trial. Patient level measures of utility derived from the EQ-5D 5L and CLDQ instruments (measured at baseline 3 and 6 months then 6-monthly in the intervention group and at the end of trial in both groups) will be integrated with survival curves in order to calculate QALYs over the study period. This economic evaluation will include cost-effectiveness, acceptability, net benefit and expected net loss curves to inform decision makers of the optimal strategy at any given threshold, and uncertainty around this decision.

At the end of the study, both groups will be asked to complete a short resource use questionnaire asking patients to share how much time and money have been spent on health care over the past 2 weeks.

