**Preliminary studies of CDM models in CLD**

CLD would appear to be a logical choice for CDM style interventions. It is characterized by frequent, lengthy and costly admissions and has effective but poorly implemented evidence-based treatment. However, it remains unclear if findings from other disease trials can be adapted to the unique challenges of CLD which include; high short term mortality, high rates of drug and alcohol addiction, frequently social disadvantage and marginalization from health care and multiple aetiologies and clinical presentations. The urgent need for RCTs has been highlighted by editorials in high impact gastroenterology journals ([25](#_ENREF_25), [26](#_ENREF_26)). However, the only RCT published to date has been a pilot trial performed by [name] et al ([27](#_ENREF_27)) and subsequently editorialized by high impact gastroenterology journals ([28](#_ENREF_28), [29](#_ENREF_29)). In this single centre trial of 60 patients a multifaceted CDM model was used during a 12 month period. The main components of this intervention were delivery system re-design (co-ordinated case-management, home visits, weekly telephone reviews, rapid access to care pathways) and increase self-management support (patient action plans, increased education and self-monitoring, medication blister packs).

The major findings of this pilot trial were:

- No reduction in the primary endpoint of liver-related occupied bed day rates in the intervention versus usual care arms (17.8 vs 11.0 bed days/person/year, incidence rate ratio=1.6, 95% CI=0.5-4.8, P=0.39), however a non-significant 21 % reduction in unplanned/emergency admissions
- Non-significant reduction in mortality in intervention arm (Hazard ratio 0.6, 95% CI=0.3-1.5, P=0.32)
- Significantly improved quality of life for intervention patients relative to baseline but no significant improvement relative to usual care group
- Significantly improved quality of care in intervention group for outpatient attendance and adherence to protocols for HCC screening, vaccination and bone density surveillance.
- Cost effectiveness was demonstrated in a subsequent analysis which showed the intervention was less expensive per patient by a mean of $ 57,000 per participant with a 96 % probability of cost effectiveness at a willingness to pay of $ 40,000 per death avoided ([30](#_ENREF_30)).

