## Outpatient review by Specialist Gastroenterologist/Hepatologist

Review by a specialist must be scheduled within 1 month (4 weeks) of discharge from hospital for all patients in the intervention group. The nurse must attend this appointment with the patient. In preparation for the outpatient appointment the following should be updated:

- - Medication list
  - Care Plan
  - Ensure screening and surveillance requirements are up to date (or booked)

At this appointment the specialist will discuss the care plan with the nurse and the patient and sign off on the care plan.

## Month 3, Month 6, Month 12, Month 18

Patients in the intervention group have their Child Pugh and Meld scores completed at 3, 6, 12, 18 months and at end of trial (Appendix N). Collect the information from the most recent bloods taken as part of usual care, the patient will not be required to have a blood test taken just for this score to be done.

Surveys are due for both groups at this time. For intervention patients this should ideally be scheduled at the same time the specialist outpatient appointment is scheduled to enable accurate determination of the Child Pugh and MELD score. Ensure the contact log is up to date. Patients will be provided the option of receiving the surveys via standard post or electronically, via email, at consent.

Record hospital and liver-related outpatient admissions/attendances/non attendances at the month 12 visit.

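### No cost source is named for public hospital outpatient care or non-admitted tests, which the intervention is designed to increase, so its incremental cost is likely to be understated

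*Protocol*

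**What the plan says.** The Protocol section on incremental cost effectiveness and quality of life builds the cost difference between the arms from these sources:

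- MBS and PBS data, used "to estimate primary care, pharmaceutical, and private hospital costs".
- AR-DRG cost weights, described as "centralised costing data for inpatient episodes at public hospitals".
- Trial records: "Intervention specific costs (e.g. labour costs, travel and telephone expenditure etc) will be collected administratively within the trial".
- At the end of the study, a "short resource use questionnaire asking patients to share how much time and money have been spent on health care over the past 2 weeks". The activity schedules also place this questionnaire at baseline.

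Consent is sought for PBS, MBS and AR-DRG data. The primary economic outcome is the "incremental cost per unplanned admission avoided in the intervention arm relative to the usual care arm". Cost per death prevented and cost per QALY are secondary and share the same numerator.

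On outpatient care, the visit procedures state: "Review by a specialist must be scheduled within 1 month (4 weeks) of discharge from hospital for all patients in the intervention group". The intervention schedule has a hepatologist outpatient row marked at Months 3, 6, 12, 18 and 24/end of study. The control schedule has no such row, though it does record liver-related appointments at Month 12 and end of study. Under Role of CLD nurse, the nurse arranges outstanding investigations and helps the patient attend appointments. Of the pilot, the background reports: "Significantly improved quality of care in intervention group for outpatient attendance".

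**The concern.** Each source has a stated scope, and public outpatient care falls outside all of them. Public clinic reviews, and imaging, endoscopy or allied health at a trial hospital without admission, are not primary care, medicines, private hospital care or public inpatient episodes. Emergency attendances that do not lead to admission are not named either.

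This matters because clinic reviews and surveillance tests are part of how the intervention is meant to work. If the costing is done as written, the numerator of all three economic ratios leaves out a cost that the intervention is designed to raise. A decision maker would then see the model as somewhat cheaper than it is.

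**Working it through.** The protocol states no cost total, so there is no figure to reproduce. The check compares the cost sources with the care delivered and then illustrates the size.

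**Coverage of each source**

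| Source | Covers public outpatient visits or non-admitted tests? |
| --- | --- |
| MBS/PBS | Not within the stated scope. Some tests might still appear as MBS claims; the protocol does not say. |
| AR-DRG weights | Inpatient episodes only. A day-case endoscopy might count as an episode; the protocol does not say. |
| Intervention costs | Examples are labour, travel and telephone. The nurse's time at a clinic visit fits here; the visit itself does not. |
| Patient questionnaire | Patients' own time and money over two weeks. It cannot cost hospital visits over 24 months. |
| Appendix K log | Kept in both arms, with date, attendance and reason for non-attendance. It has no appointment type, and nothing links it to costing. Attendance is used as a quality indicator. |

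**Visits required by the intervention**

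- Review within 4 weeks of discharge: 1.
- Scheduled hepatology visits at Months 3, 6, 12, 18 and 24: 5.
- Total: 1 + 5 = 6 per patient followed to 24 months, and 1 + 4 = 5 by Month 18.

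Only the difference between arms enters the incremental cost. Six extra visits would require controls to have no clinic visits at all, so six is an upper bound.

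**Illustrative size**

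The documents give neither the number of extra visits nor a unit cost. Assume 1 to 6 extra visits at A$100 to A$500 each.

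- Uncounted cost per intervention patient: 1 × 100 = A$100, up to 6 × 500 = A$3,000.
- Against the pilot's mean difference of $57,000 per participant: 100/57,000 = 0.2%, up to 3,000/57,000 = 5.3%.

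Shift in the primary ratio = uncounted cost ÷ admissions avoided. Admissions avoided per patient = 3 per year × 0.20 × years, from the sample size section's assumed control rate and reduction.

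- 24 months: 3 × 0.20 × 2 = 1.2 avoided. Shift from 100/1.2 = A$83 to 3,000/1.2 = A$2,500 per admission avoided.
- 18 months (the planned median follow-up): 3 × 0.20 × 1.5 = 0.9 avoided. With at most five visits, shift from 100/0.9 = A$111 to 2,500/0.9 = A$2,778.

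Investigations are not priced here and would add to these figures where they are not already captured.

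**The case against.** The strongest reply is that the list of sources is not stated to be exhaustive, and that a full resource inventory with unit costs normally belongs in an analysis plan, which is not available here. That is fair as to detail. It does not remove the point, because the protocol does more than stay silent: it assigns each source a scope, and the data requests and consent follow from that scope.

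Four stronger readings are tempting, and the documents do not support them:

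- **All this care is costed at zero.** A reader might infer this, but some tests may be in MBS claims and some procedures may be day-case episodes. The gap is clear for public clinic visits and less clear for tests.
- **Outpatient cost rose in the pilot.** The pilot result is better attendance as a quality indicator. It could reflect fewer missed appointments, and no outpatient cost is reported.
- **Controls have no clinic visits.** The control schedule lists trial activities. Under Control/usual care group and Role of Gastroenterologist/Hepatologist, usual care continues and the usual specialists see both arms.
- **The error cannot be repaired later.** Outpatient appointments are logged in both arms, so unit costs can be applied afterwards to much of the omitted care. Non-admitted emergency visits have no trial log.

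A reader might also set the omission against nurse cost, which makes it look large. That needs an assumed salary, and nurse cost is not the incremental cost. The net direction is not certain either: if the intervention reduces emergency attendances without admission, leaving those out works against it.

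**Conclusion.** The point holds as a gap in the costing. Public hospital outpatient attendances, and imaging, endoscopy and allied health outside an admission, have no assigned cost source in either arm, and neither the intervention costs nor the questionnaire fills it. Because the intervention requires clinic reviews and promotes investigations, an understated incremental cost is the likely result, but it is an inference. The size cannot be derived from the documents. Under the assumed visit counts and prices it is A$100 to A$3,000 per intervention patient, at most about 5% of the pilot difference. That pilot was a single-centre study of 60 patients over 12 months, so the percentage is only a guide. A shift of this size might not change the sign of the cost difference. The economic evaluation is a secondary objective, and the primary clinical endpoint is unaffected. The gap should be closed because it sits in the numerator of all three ratios and is cheap to repair.

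**What to change.** In the economic outcomes section, add three items to the costed resources in both arms: public hospital outpatient attendances, investigations done outside an admission, and emergency attendances without admission. There are two routes:

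1. Widen the planned hospital costing extract to non-admitted care, extending the consent wording if needed. This is the route that also reaches emergency attendances.
2. Apply standard non-admitted unit costs to the Appendix K log, after adding a field for appointment type (medical, allied health, radiology, endoscopy, the categories already listed under Quality of care indicators).

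Whichever is used, check against MBS claims and day-case episodes so that nothing is counted twice, and vary the unit costs in the one-way and multi-way sensitivity analyses already planned under Statistical methods.

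The cost is a little more data work, a short addition to the protocol, and a cost difference that may look less favourable to the intervention.

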## Control/usual care group

Control/usual care patients will continue hospital and out of hospital management via usual care processes. To prevent contamination of usual care patients by the intervention, usual care patients will have no contact with CLD nurses until a final end of study interview. Usual care patients will be mailed surveys at baseline, 3 months, 6 months, and then 6-monthly until the end of the trial (24 months after the first patient randomised). At the end of the trial, control group participants are invited for a face-to-face review to complete the surveys, are given the Cirrhosis Booklet and offered an education session.

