### Baseline – all patients

Patients in the intervention and control group will have the following collected using the Baseline collection tool (Appendix A):

- - Demographics
  - Aetiology of cirrhosis
  - Child Pugh/MELD Score
  - All surveys (PIH, CLDQ, Cirrhosis Knowledge Assessment Questionnaire, EQ-5D-5L, ASK-12, and resource use survey)
  - Concomitant medication list (as per current hospital medication chart)
  - Comorbidities list and the Charlson Comorbidity index

Once all of the baseline information is collected Randomisation occurs via the telephone contact.

If a patient has been randomised to receive usual care, please advise them that they will be receiving future surveys by mail and that at the end of the trial they will be invited to come in for a face to face meeting and education. Ensure their address and contact details are correct.

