## Mortality and disease severity

Mortality at end of study follow up will be a further secondary endpoint of the study. To ensure patients lost to follow up have not died, cross checking with Australian death registries will occur. Other clinically relevant indicators of liver disease severity MELD and Child Pugh score, will also be monitored at baseline, study end and 3-monthly during the trial period.

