## Statistical methods

All analyses will be performed according to an intention-to-treat protocol. Differences between groups for hospitalization rates, quality indicators, satisfaction rates and self-management scores will be assessed using negative binomial regression, which is appropriate for count data with evidence of over-dispersion. All models will allow adjustment for baseline values and other co-variates. Suitable transformations will be applied in the case of non-normally distributed data.

For the economic analysis mean costs between the intervention and control groups will be compared and incremental cost effectiveness ratios presented with confidence intervals. Cost effectiveness acceptability curves for varying threshold values of cost effectiveness will also be presented ([46](#_ENREF_46)). An assessment of the sensitivity of the results obtained to variation in measured resource use, effectiveness and/or unit costs will be undertaken using appropriate one-way and multi-way sensitivity analysis ([47](#_ENREF_47)). Differences between groups in quality of life scores will be assessed using mixed effects regression to account for the repeated measures (every 3 months) and subsequent within-Participant correlation. Survival analysis will be performed using Cox regression with results presented as Kaplan-Meir survival curves.

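### The economic section's utility schedule, with repeated measures in the intervention arm and only an end-of-trial value in controls, contradicts the survey schedule the protocol sets for both arms

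*Protocol*

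**What the plan says.** **Utilities for the QALY.** Under *Incremental cost effectiveness relative to usual care and quality of life*, EQ-5D-5L and CLDQ utilities are "measured at baseline 3 and 6 months then 6-monthly in the intervention group and at the end of trial in both groups", and they "will be integrated with survival curves in order to calculate QALYs over the study period". No other section says which utilities enter the QALY.

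**Survey collection.** Other sections give controls the full schedule:
- *Baseline – all patients*: "Patients in the intervention and control group will have the following collected using the Baseline collection tool", and the list includes "All surveys (PIH, CLDQ, Cirrhosis Knowledge Assessment Questionnaire, EQ-5D-5L, ASK-12, and resource use survey".
- *Control/usual care group*: "Usual care patients will be mailed surveys at baseline, 3 months, 6 months, and then 6-monthly until the end of the trial".
- *Month 3, Month 6, Month 12, Month 18*: surveys fall due in both groups at these visits.
- *Activity Schedule for CONTROL patients*: the survey row is marked at baseline and months 3, 6, 12, 18 and 24/EOS, as in the intervention table.

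**Quality-of-life analysis.** *Statistical methods* plans a between-group comparison by "mixed effects regression to account for the repeated measures (every 3 months").

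**Disease severity.** *Mortality and disease severity* says that MELD and Child-Pugh "will also be monitored at baseline, study end and 3-monthly during the trial period", with no limit to one arm. The month 3 to 18 visit section says: "Patients in the intervention group have their Child Pugh and Meld scores completed at 3, 6, 12, 18 months and at end of trial". The control schedule marks these scores at baseline and month 24/EOS only, and Appendix N carries an intervention-only label among its interim time points.

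**The concern.** A QALY is an area under a utility curve weighted by survival, so it depends on when utility is measured as well as on utility itself. If one arm's curve has six points and the other's has one, the two areas can differ although the patients fare identically. That difference would pass straight into the incremental cost per QALY and could not be told apart from a treatment effect.

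This is not a detail the protocol leaves to a statistical analysis plan. The economic section fixes the time points by arm, and fixes them differently from the rest of the document. An analyst or health economist working from that section alone would have grounds to leave out control data that the trial collects.

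The severity scores raise a separate issue of the same kind. They are listed as clinically relevant indicators, but as scheduled they allow no between-arm comparison between baseline and end of study.

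**Working it through.** The protocol gives no utility values and no QALY figure, so there is nothing of its own to reproduce. The check has three parts.

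**1. Time points by section (months)**

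| Protocol section | Intervention | Control |
|---|---|---|
| Economic section, as worded | 0, 3, 6, then 6-monthly, end | end only |
| Baseline, control-group and month 3–18 sections | 0, 3, 6, 12, 18, 24 | 0, 3, 6, 12, 18, 24 |
| Activity schedules, survey row | 0, 3, 6, 12, 18, 24 | 0, 3, 6, 12, 18, 24 |
| Statistical methods (quality of life) | every 3 months | every 3 months |

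The survey row counts five surveys without naming them. The baseline list has six, and the resource use survey has its own row. The remaining five include EQ-5D-5L and CLDQ. Neither schedule has surveys at months 9, 15 or 21, so measurement every 3 months is delivered in neither arm.

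**2. What the literal reading could do**

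Give both arms the same assumed utility path, so that the true effect is zero, and assume no deaths over two years.
- Intervention: trapezoid rule, sum of (t₂ − t₁) × (u₁ + u₂)/2 over the six points.
- Control: the one end value held for two years, 2 × u(24). This is itself an assumption, because a single point defines no curve.

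Worked example, dip then late decline (0.50, 0.65, 0.70, 0.70, 0.65, 0.60):
- Intervention: 0.25 × 0.575 + 0.25 × 0.675 + 0.5 × 0.700 + 0.5 × 0.675 + 0.5 × 0.625 = 1.3125.
- Control: 2 × 0.60 = 1.200.
- Difference: +0.113.

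| Assumed path, same in both arms | Six points | End only | Intervention − control |
|---|---|---|---|
| Flat 0.65 | 1.300 | 1.300 | 0.000 |
| Linear decline 0.70 to 0.50 | 1.200 | 1.000 | +0.200 |
| Linear rise 0.50 to 0.70 | 1.200 | 1.400 | −0.200 |
| Dip then plateau (0.50, 0.65, then 0.70) | 1.3625 | 1.400 | −0.038 |
| Dip then late decline | 1.3125 | 1.200 | +0.113 |

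The economic section combines utilities with survival, so deaths matter. The *Background* gives two-year survival of 60% (Child-Pugh B) and 35% (Child-Pugh C). Weight utility by S(t) = exp(−ht), with h = −ln(0.60)/2 or −ln(0.35)/2, and assume that utility is unrelated to risk of death. The dip-then-late-decline difference then becomes +0.088 or +0.068. Deaths shrink the artefact in this example but do not remove it.

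With the same six points in both arms the difference is 0.000 for every path, because the two calculations are then identical.

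**3. MELD and Child-Pugh**

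The outcomes section says 3-monthly with no arm limit. The visit section, both activity schedules and Appendix N give the intervention arm 0, 3, 6, 12, 18 and 24 months, and controls 0 and 24/EOS. So neither arm is scored 3-monthly, and only baseline and end of study can be compared between arms. These scores do not enter the QALY, which is built from EQ-5D-5L, CLDQ and survival.

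**The case against.** The strongest reply is that control utilities are planned and collected. Four places in the protocol say so, and the mixed model for quality of life needs them. Bias would arise only if someone discarded data already in hand, and on the operating schedule the artefact is zero. This stands, and it makes the point an internal contradiction rather than a biased design.

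The sentence could also be parsed more loosely, with baseline, 3 and 6 months applying to both groups. That would narrow the conflict but not remove it, since controls would still lack months 12 and 18.

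A reader might go further and infer a false gain favouring the intervention, because patients recruited in hospital should recover early. For example, take 0.55 at baseline and 0.70 from month 3 in both arms. Six points give 0.25 × 0.625 + 1.75 × 0.70 = 1.381. A straight line from baseline to end gives 2 × 0.625 = 1.250, an apparent gain of 0.131. The documents do not support this:
- A baseline-plus-end control schedule is stated nowhere. On the literal end-only reading, the same utilities give 2 × 0.70 = 1.400, a difference of −0.019 against the intervention.
- The protocol says nothing about early recovery of utility, and it also recruits from outpatient clinics.

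A reader might also infer that intervention-only severity scores bias the QALY. They cannot, since they are not an input to it.

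**Conclusion.** The contradiction is real. The one section that defines the QALY inputs is wrong as worded when set against the rest of the protocol. Followed literally, it could produce a QALY difference with no true effect. With end-only controls, no deaths and the assumed paths above, that difference lies between about −0.20 and +0.20 QALY per patient over two years. Its sign and size depend on a utility path that the protocol does not give, so no single figure or direction should be quoted.

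The every-3-months statement and the MELD/Child-Pugh mismatch are also confirmed; the second is separate from the QALY. Cost per QALY is a secondary economic outcome. The primary endpoint (unplanned liver-related admission rate) and the primary economic outcome (cost per unplanned admission avoided) are unaffected. The protocol should be corrected, but the matter is moderate.

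**What to change.** 1. **Economic section.** State that QALYs in both arms use utilities from baseline and months 3, 6, 12, 18 and 24, with the same calculation rule in both arms. The surveys are already scheduled, so this costs only wording.
2. **Statistical methods.** Replace the every-3-months frequency for quality of life with that schedule. This is also wording only.
3. **Mortality and disease severity.** Reconcile this section with the visit section, both activity schedules and Appendix N, in one of two ways:
   - Limit the between-arm severity comparison to baseline and end of study, and state the interim scores as intervention-only at months 3, 6, 12 and 18.
   - Abstract control MELD at months 3, 6, 12 and 18 from usual-care bloods in the hospital record. Derive Child-Pugh only where ascites and encephalopathy grade are documented, because Appendix N needs both and blood results alone do not supply them.

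The first option costs nothing but gives up interim comparison. The second needs some record abstraction, with no extra blood test and no nurse contact with controls. Its weakness is that bloods may be available less evenly in one arm than in the other, so availability by arm should be reported alongside the scores.

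### No adjustment for baseline EQ-5D-5L is stated for the incremental QALY, although it is measured in both arms before randomisation; adjusting would gain modest precision at no data cost

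*Protocol*

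**What the plan says.** The Outcomes section on incremental cost effectiveness makes cost per QALY a secondary economic outcome: "Secondary economic outcomes will include the incremental cost per death prevented and incremental costs per quality adjusted life year (QALY) gained". It bases QALYs on the EQ-5D-5L and the CLDQ, and fixes how they are formed: patient-level utilities "will be integrated with survival curves in order to calculate QALYs over the study period". No covariate is mentioned.

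The economic paragraph of Statistical methods begins "For the economic analysis mean costs between the intervention and control groups will be compared" and goes on to incremental ratios with confidence intervals, acceptability curves and sensitivity analyses. It names no covariate either. Earlier in that section, directly after the outcomes assigned to negative binomial regression, a general sentence lets all models adjust for baseline values and other covariates. Quality-of-life scores have their own mixed effects analysis, which is not linked to the QALY.

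On collection, the section Baseline – all patients covers both groups and lists "All surveys (PIH, CLDQ, Cirrhosis Knowledge Assessment Questionnaire, EQ-5D-5L, ASK-12, and resource use survey"; randomisation follows once baseline data are complete. Appendix A agrees, and the control schedule has surveys at baseline. The section on the control group says: "Usual care patients will be mailed surveys at baseline, 3 months, 6 months, and then 6-monthly until the end of the trial". The cost-effectiveness section describes its utility measures differently: "measured at baseline 3 and 6 months then 6-monthly in the intervention group and at the end of trial in both groups".

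**The concern.** Baseline utility is the first point of each patient's utility curve and usually predicts the later points. If one arm happens to start with higher utility, part of that head start is counted as QALYs gained. Nothing in the design balances utility: stratification is by aetiology only, and the background section on the indication for the trial itself notes that the small pilot was open to chance imbalance in aetiology.

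The protocol commits to one construction of the QALY, and that construction has no stated place for the baseline value. The covariate that would remove the imbalance is already being collected. At stake are the precision of the incremental QALY and of the net-benefit and acceptability curves built on it, and the chance to fix the estimator before an adjusted and an unadjusted cost per QALY can be compared. The primary endpoint and the primary economic outcome (cost per unplanned admission avoided) are not affected.

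**Working it through.** The protocol gives no utility SD, QALY difference or QALY power, so there is no figure of its own to reproduce. What follows is an illustration.

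**Inputs from the protocol.** 75 patients per arm (Randomization, stratification, blinding); 24 months per patient (Intervention period); 2-year survival of 60% in Child-Pugh B and 35% in Child-Pugh C (Background).

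**Assumptions.** Utility SD 0.20-0.30, the same at baseline and for mean utility while alive; slope of later on baseline utility 0.4-0.6; mean utility 0.6-0.8; exponential survival; utility independent of survival; no censoring. A patient's QALY is mean utility while alive times time alive, T, within 2 years.

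**Step 1: chance baseline imbalance.** SE = SD × √(2/75).
- SD 0.20: 0.033
- SD 0.30: 0.049

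A difference larger than one SE occurs in about one trial in three.

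**Step 2: time alive over 2 years.** Hazard h = −ln(S)/2; E[T] = (1 − S)/h; E[T²] = 2 × [1 − S(1 + 2h)]/h²; Var(T) = E[T²] − E[T]².

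| 2-year survival S | h | E[T] | E[T²] | Var(T) |
|---|---|---|---|---|
| 0.60 | 0.255 | 1.57 | 2.87 | 0.41 |
| 0.35 | 0.525 | 1.24 | 2.05 | 0.52 |

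**Step 3: shift in the QALY difference from a one-SE imbalance.** Shift = slope × SE × E[T].
- Lowest: 0.4 × 0.0327 × 1.24 = 0.016
- Highest: 0.6 × 0.0490 × 1.57 = 0.046

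**Step 4: variance of a QALY and SE of the difference.** Var(Q) = SD² × E[T²] + mean² × Var(T); SE = √(2 × Var(Q)/75).
- Smallest (S 0.60, SD 0.20, mean 0.6): Var(Q) = 0.264, SE = 0.084
- Largest (S 0.60, SD 0.30, mean 0.8): Var(Q) = 0.523, SE = 0.118

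**Step 5: variance removed by adjustment.** Share = slope² × SD² × E[T]² / Var(Q).
- Lowest (S 0.35, SD 0.20, mean 0.8, slope 0.4): 0.0098/0.413 = 2.4%
- Highest (S 0.60, SD 0.30, mean 0.6, slope 0.6): 0.0795/0.407 = 19.5%

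Of the 16 combinations of end values, 14 lie below 14%. In interval width the extremes are 1 − √(1 − 0.024) = 1% and 1 − √(1 − 0.195) = 10%.

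**Measurement schedule.** Set beside the sections on baseline and on the control group, the parenthesis in the cost-effectiveness section puts baseline and interim utilities in the intervention group and both groups together only at the end. Taken literally, it would leave control QALYs without a starting value or a curve, and baseline adjustment could not be done.

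**The case against.** The strongest reply is that this is silence and not error. Covariates for a QALY comparison are commonly left to a statistical or health-economic analysis plan, which is not at hand, and nothing in the protocol forbids adjustment. The general sentence on baseline values might be meant to cover it. Much of this stands, and it keeps the point modest. What remains is that the protocol does fix a QALY method, that the method as written has no baseline term, and that the general sentence sits with the count regressions, ahead of the economic paragraph.

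Four stronger readings are tempting, and the documents do not support them.
- A reader might infer that the cost per QALY is biased. Under randomisation the unadjusted difference is unbiased; chance imbalance is sampling error, already inside the promised confidence intervals.
- A reader might infer that arm-level survival curves are used and unadjusted QALY means compared. The text says only survival curves, with patient-level utilities, and the means that Statistical methods compares are costs.
- A reader might expect a variance reduction of 16-36%, the square of a correlation of 0.4-0.6 between baseline utility and the QALY. At the protocol's own survival rates, time alive supplies much of the QALY variance, and the reduction is smaller.
- A reader might conclude from the parenthesis that controls have no baseline utility. The baseline section, the control-group section, the activity schedule and Appendix A all say otherwise.

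**Conclusion.** The point holds as a modest improvement to a secondary economic outcome. No baseline-utility adjustment is stated for the incremental QALY, and the data for it are planned in both arms. Under the assumptions above, a one-SE baseline imbalance moves the QALY difference by about 0.016-0.046, against a standard error of about 0.08-0.12, and adjustment cuts the variance by about 2-20%.

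These sizes rest on assumed utility figures that the protocol does not supply and on utility being independent of survival; if baseline utility also predicts survival, the gain would be larger. The contradictory measurement schedule is the firmer textual problem, because both the control QALYs and the adjustment depend on how it is resolved.

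**What to change.** State in the cost-effectiveness section and in the economic paragraph of Statistical methods that the incremental QALY is estimated by regressing patient-level QALYs on arm, baseline EQ-5D-5L utility and aetiology stratum, and is bootstrapped jointly with cost for the acceptability and net-benefit curves.

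Utility is set to zero from death. Censoring at loss to follow-up or transplant listing must be handled, for example by inverse-probability weighting or multiple imputation, because plain per-patient areas under the curve would ignore the censoring that the survival-curve step takes into account. Keep the survival-curve calculation as a check.

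In the same edit, reconcile the parenthesis on when utilities are measured with the baseline section, the control-group section and the activity schedule, so that one schedule applies to both arms.

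The cost is a little more analysis work. No new data are needed, provided EQ-5D-5L is collected in both arms as those sections already plan.
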